#### Specimen processing

Blood and tissue specimens collected in the course of this research project may be banked and used in the future to investigate new scientific questions related to this study and for basic studies of lymphoma biology in vitro. However, this research may only be done if the risks of the new questions were covered in the consent document. If new risks are associated with the research (e.g., analysis of germ line genetic mutations) the principal investigator must amend the protocol and obtain informed consent from all research subjects.

All peripheral blood samples will be sent promptly to the Lymphoma/Myeloma Core laboratory, UTMDACC. Red top tubes will be spun down and serum divided into 1 ml aliquots and frozen. PBMCs will be isolated prior to freezing by Ficoll-Hypaque centrifugation using standard protocols.

#### Assay for serum tumor-specific antibody

Serum tumor-specific antibody will be assayed by flow cytometry. Serial dilutions of pre-immune and hyperimmune serum samples from each patient will be mixed with autologous tumor cells (or idiotype monoclonal protein when available) or isotype-matched irrelevant tumor cells (or monoclonal protein of irrelevant specificity) from a different patient. Bound anti-tumor antibody is detected with FITC labeled goat anti-human light-chain antibodies directed against the light chain not present in the immunoglobulin idiotype (Caltag Laboratories, South San Francisco). A response is considered positive when a four-fold rise in the bound antibody titer is observed compared to the pre-vaccine serum and the isotype matched irrelevant tumor used as specificity controls.

#### Assay of precursor frequency of tumor-specific cytotoxic T-lymphocytes

The precursor frequency of tumor-specific cytotoxic T-lymphocytes will be determined by modified interferon gamma (IFNγ) ELISPOT assay as described previously [32]. A three-fold rise in the frequency of tumor-reactive T cell precursors in the post-vaccine PBMC sample compared to the pre-vaccine sample will be considered positive, with a minimum precursor frequency of 1 in 80,000 cells if the precursor frequency in the pre-vaccine sample is zero [33].

#### Assay for anti-MIP-3α antibodies

Anti-MIP-3α antibodies will be assessed by direct enzyme-linked immunosorbent assay (ELISA). Pre-immune and hyperimmune serum samples from each patient will be diluted over wells of a microtiter plate that are coated with human MIP-3α. Bound antibody is detected with horseradish peroxidase-goat antihuman IgG (Caltag Laboratories, South San Francisco). A four-fold rise in the bound antibody titer in the post-vaccine serum vs pre-vaccine serum and an irrelevant human chemokine used as specificity control constitutes a positive response.

Disease response and relapse/progression will be assessed according to the criteria in the Update on Recommendations for Assessing Response from the Third International Workshop on Waldenstrom’s Macroglobulinemia [34].

### Statistical plan

DLT is defined as follows: ≥ grade 2 allergic reaction, ≥ grade 2 autoimmune reaction and any grade 3 or 4 toxicity except for fever, grade 4 fever which subsequently requires 50% dose reduction. Applying the 3 + 3 design [35], the first cohort of 3 patients will be treated at dose level 1 and evaluated for DLT at the end of the first cycle (4 weeks). Following the standard 3 + 3 design, the MTD is defined as the highest dose level in which 6 patients have been treated with less than 2 instances of DLT [35]. Given 2 predefined dose levels, it is anticipated that up to 12 eligible patients are required for this dose-finding phase I trial.

If greater than 1 out of 3 patients or 1 out of 6 patients experience DLT at the lower dose level, this dose will be considered too toxic and the protocol will be stopped.

Toxicity type and severity will be summarized by frequency tables.

The secondary endpoint of immune response will estimated using the intent-to-treat population. Immune response will be defined as at least a three-fold rise in the frequency of tumor-reactive precursor T-cells in the 12 weeks post-vaccine PBMC sample compared with the pre-vaccine sample, or a minimum precursor frequency of 1 in 80,000 cells post vaccination if the precursor frequency in the pre-vaccine sample is zero.

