## Methods

### Study design

This study is a prospective clinical investigation designed to generate safety data. It is an open-label, phase I trial designed to determine the safety and tolerability of intradermal administration of patient-specific scFv-CCL20 DNA vaccine in patients with asymptomatic LPL. Patients will receive a series of 3 vaccinations at 4-week intervals (weeks 0, 4 and 8). The 2 pre-defined dose levels – Cohort 1 (500 μg DNA vaccine) and Cohort 2 (2500 μg DNA vaccine) – were chosen based on the pre-clinical experience [24, 25].

All patients will either undergo bone marrow aspiration of 10 ml or lymph node harvest prior to starting treatment to obtain cells to prepare their vaccine. Once the vaccine for a given patient is available, he or she will receive 3 doses of DNA vaccine encoding autologous lymphoma scFv- human CCL20 (MIP-3α) fusion protein.

Enrollment to Cohorts 1 and 2 will follow a standard 3 + 3 statistical design, and will thus require a maximum of 12 patients, and shall be staggered to ensure no patient is administered the vaccine until any previously exposed patient has completed a minimum of 48 h of safety follow-up after receiving the first DNA vaccine administration. Prior to advancing dose levels, a cohort summary will be completed and submitted to the IND office medical monitor for review and approval to proceed to the next cohort.

If patients have progressive disease that requires chemotherapy or radiotherapy treatment before or while receiving vaccination, vaccination will either not begin or will be stopped, and the patient will be taken off study. Patients will be vaccinated intradermally and the injection sites will be rotated between the thighs. Patients will be observed in CTRC for 2 h after vaccine administration; vital signs will be taken every 15 min during the first hour and every 30 min during the second hour. The use of non-steroidal anti-inflammatory drugs (NSAIDs) and/or steroids should be avoided during the vaccination. Should NSAIDs or steroids be required for unrelated medical conditions for a course exceeding 2 weeks, the patient will be taken off the study. Patients will receive a list of common aspirin containing products to avoid at the time of study entry. Any local skin reactions will be carefully noted and scored for erythema, induration, pain and disruption of the barrier surface.

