Toxicities will be graded according to the NCI Common Toxicity Criteria v4.0. No further vaccinations will be given to patients who develop grade 3 or 4 hypersensitivity reactions or grade 3 injection site reactions. No dose modification will be made for grade 3 fever. For grade 4 fever, subsequent vaccinations will be administered at 50% of the original dose level. For all other grade 3 or 4 toxicity reactions, no further vaccinations will be given if in the opinion of the investigator the toxicity is related to the vaccine administration.

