All patients will be registered in the Clinical Oncology Research System (CORe). All patients who have asymptomatic LPL will be seen by members of the UTMDACC Department of Lymphoma and Myeloma, and tracked by the research nurse/study coordinator in charge of this study. Participation on this protocol will be discussed with patients deemed eligible. Formal screening for eligibility will occur if informed consent is received. The informed consent document is included in the Supplementary Data. For eligible patients not enrolled on the study, a Health Insurance Portability and Accountability Act (HIPAA) compliant pre-enrollment and enrollment log will be maintained in CORe to track reason(s) for lack of enrollment. The patient’s entry date on protocol will be the day the patient is registered in CORe. The treatment start date will be the day the first dose of vaccine is administered to the patient.

Patients will be removed from protocol for any of the following reasons: adverse event(s) occur that in the judgment of the investigator, may cause severe or permanent harm or which rule out continuation of study drug; the patient declines further therapy, experiences progression of LPL that requires initiation of systemic therapy to control symptoms, or has an inadequate number of biopsy cells (< 1.0 × 10^9^) for vaccine manufacture or there is an unforeseen vaccine manufacturing failure. Additionally a patient will be removed from protocol if it is deemed in their best interest, in which case the Principal Investigator should be notified, and the reasons for withdrawal should be noted in the flow sheet.

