### Study drug

The scFv-CCL20 plasmid DNA vaccine is prepared from the VH and VL lymphoma immunoglobulin variable regions of each patient’s tumor cells in three cloning steps [31]. First, the individual VH and VL are cloned by RT-PCR using consensus primers. The mature V region sequences are then cloned in-frame with a short linker to yield a single chain antibody gene (scFv). Lastly, the scFv gene sequence is cloned in-frame to the 3′ end of the human CCL20 (MIP-3α) gene via a spacer sequence. At each stage the DNA sequences are verified. The plasmid DNA is then amplified in *E coli,* and subsequently purified from *E coli* according to Good Manufacturing Practices (GMP) standards and tested for sterility and endotoxin contamination prior to its use in any patient. The entire vaccine preparation procedure takes 12 months and is conducted at FUJIFILM Diosynth Biotechnologies U.S.A., Inc., GMP facility.

The drug is formulated on a 0.5 ml basis with patient-specific scFv-CCL20 plasmid DNA vaccine. Each patient-specific formulation will have 500 μg or 2500 μg of the plasmid DNA depending on the cohort assignment of the patient. Each vial of patient-specific vaccine will be labeled with the following information: scFv-CCL20 DNA vaccine, patient last name and first initial, patient-specific lot, final volume, storage conditions, and fill date. The protocol number, drug strength, expiration date, and the statement, “Caution: New drug – Limited by Federal law to investigational use,” will also appear on the vaccine vial label.

Prior to administration the vaccine will be stored at − 20 °C. Immediately prior to dosing, the contents of the vial will be thawed to room temperature. After gentle agitation, the vial contents should be drawn up using a filling adaptor attached to a syringe for the Tropis™ intradermal needle free injection device. After the contents of the vial have been drawn up, the syringe assembly will be inserted into the needle free injector. The vial adaptor will then be removed, and the vaccine will be administered by needle-free injection device for intradermal injection in the thighs. The syringe should be refrigerated at 2 °C to 8 °C and the vaccine will be administered in a total volume of 0.5 mL. Due to the 0.1 ml volume limit of the Tropis™ intradermal needle free injection device, the total volume of 0.5 ml will be administered in 5 injections.

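### Grade 2 allergic and autoimmune reactions count as DLTs, but no printed rule holds the affected patient's next full-dose vaccination

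*Protocol article*

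**What the plan says.** **DLT definition (Statistical plan).** "DLT is defined as follows: ≥ grade 2 allergic reaction, ≥ grade 2 autoimmune reaction", together with grade 3 or 4 toxicity other than fever, and grade 4 fever. DLTs are evaluated at the end of the first 4-week cycle.

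**Dosing rules for the individual patient (Study design).**
- "No further vaccinations will be given to patients who develop grade 3 or 4 hypersensitivity reactions or grade 3 injection site reactions".
- "For grade 4 fever, subsequent vaccinations will be administered at 50% of the original dose level". Grade 3 fever changes nothing.
- "For all other grade 3 or 4 toxicity reactions, no further vaccinations will be given if in the opinion of the investigator" the event is attributed to the vaccine.

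**Schedule and dose (Study design, Study drug).** Vaccinations fall at weeks 0, 4 and 8, at 500 or 2500 μg each. For each vaccination, "the total volume of 0.5 ml will be administered in 5 injections".

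**Discretion (Patients).** A patient is removed for adverse events that "in the judgment of the investigator, may cause severe or permanent harm or which rule out continuation of study drug", or when removal is thought to be in the patient's best interest. Neither ground is tied to a grade.

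**Medical review (Study design).** Before the dose level is raised, a cohort summary is "submitted to the IND office medical monitor for review and approval to proceed to the next cohort".

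**The concern.** The plan singles out allergic and autoimmune reactions as special hazards. They are the only toxicities whose DLT threshold is lowered to grade 2. Patients with positive ANA or anti-dsDNA, or with most autoimmune histories, are excluded, and Table 1 repeats the antibody tests at every vaccine visit. Yet the list of dosing actions, including its catch-all, begins at grade 3. An event the plan calls dose-limiting then has no stated effect on that patient's dosing.

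With immune-mediated reactions the next exposure is the main worry. Vaccination 2 is due at week 4, just as the 4-week DLT evaluation ends, so the decision to re-expose comes at once and rests on the investigator's judgment, with no required hold or second opinion. These are asymptomatic patients in a first-in-human trial who would otherwise be observed. The stake is individual safety, not the operating characteristics of the 3 + 3 design.

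**Working it through.** **1. The plan's own figure.** Two dose levels × 6 patients = 12, as the Statistical plan states. Nothing below changes it.

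**2. DLT categories against dosing actions.**

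| Event | DLT? | Printed dosing action |
|---|---|---|
| Grade 2 allergic | yes | none |
| Grade 2 autoimmune | yes | none |
| Grade 3–4 allergic (hypersensitivity) | yes | stop |
| Grade 3–4 autoimmune | yes | stop if judged related |
| Grade 3 injection site | yes | stop |
| Other grade 3–4, not fever | yes | stop if judged related |
| Grade 4 fever | yes | 50% dose |

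Only the first two rows have no rule at all. The DLT definition speaks of allergic reactions and the dosing rules of hypersensitivity. Even if these are read as different events, no rule covers grade 2 of either.

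**3. Exposure left on the default schedule.** Inputs: 3 vaccinations, 5 injections each, 500 or 2500 μg per vaccination.
- Event after vaccination 1: 2 × 5 = 10 of 15 injections; 2 × 2500 = 5000 of 7500 μg, or 2 × 500 = 1000 of 1500 μg.
- Event after vaccination 2: 5 of 15 injections; 2500 of 7500 μg, or 500 of 1500 μg.
- Event after vaccination 3: none.

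**4. How often it could arise.** The Discussion reports 6 patients treated, so at most 12 − 6 = 6 remain. The article gives no event rate, so the rates p are assumptions. P(at least one) = 1 − (1 − p)^6; expected number = 6p.

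| Assumed p | P(at least one in 6) | Expected patients |
|---|---|---|
| 1% | 5.9% | 0.06 |
| 2% | 11.4% | 0.12 |
| 5% | 26.5% | 0.30 |
| 10% | 46.9% | 0.60 |
| 20% | 73.8% | 1.20 |

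The Study drug section expects minimal toxicity, which points to the upper rows.

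**5. Whether other provisions close the gap.**
- The removal criteria have no defined trigger, and a grade 2 event may not meet the adverse-event ground.
- Expedited reporting (Safety and adverse events) is tied to seriousness, so a non-serious grade 2 event need not reach the IND office by that route.
- The monitor's review precedes a rise in dose level. It does not govern one patient's next dose, and above the higher level there is nothing to advance to.
- The protocol stop for more than one DLT names only the lower dose level. There the gap mainly concerns a single affected patient.

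**The case against.** The strongest reply is that a threshold for cohort escalation and a threshold for stopping one patient need not match, and may differ on purpose. The article itself separates the two: after grade 4 fever, a DLT, dosing continues at half dose, and a grade 3 or 4 event judged unrelated can be a DLT with no stop. Removal by judgment is worded as mandatory once the judgment is made, and evaluations within 48 h before each vaccination give the occasion for it. Entry exclusions, 2 h of observation and staggered first dosing add protection. Much of this stands. It makes the gap narrower and less exceptional than a bare comparison of grades suggests. It does not remove the gap: in those other cases a printed rule tells the investigator what to do or what to judge, and for the two grade 2 DLTs there is none.

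A reader might infer that the plan orders full-dose re-vaccination after such a DLT. It does not. The dosing rules are silent, and continuation follows only from the general schedule. A reader might also infer that the MTD determination is compromised. The documents do not support that either, because the event is counted as a DLT whatever happens to the next dose.

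It is tempting to carry the 50% fever dose over to these reactions. Nothing in the article supports halving as a remedy for allergic or autoimmune re-exposure. A hold without any attribution clause would also treat a clearly unrelated grade 2 event more strictly than an unrelated grade 3 or 4 event.

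**Conclusion.** The point holds as a minor patient-safety gap. Two printed thresholds for the same kind of reaction differ by one grade, and between them lies a DLT with no hold. For an affected patient, up to two thirds of the planned course remains scheduled at full dose. Across the trial the expected gain from a fix is small: 0.06 to 0.12 affected patients at assumed rates of 1% to 2%, and 0.60 at 10%. These figures are upper bounds on the benefit, since they take all 6 remaining patients as still to be dosed and give no credit for holds the investigator would impose anyway. The two-thirds figure applies only to events after vaccination 1. The DLT count, MTD rule and sample size do not change.

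**What to change.** Add one sentence to the dosing rules under Study design: after a grade 2 allergic (hypersensitivity) or grade 2 autoimmune reaction following any vaccination, unless judged clearly unrelated to the vaccine, the next vaccination is withheld and resumes only if the event has resolved and the IND office medical monitor approves. Tying the rule to the event rather than to the 4-week DLT evaluation also covers a reaction after vaccination 2. Do not prescribe a 50% resumption dose. Use one term for allergic reaction and hypersensitivity in Study design and Statistical plan. If the different thresholds are intended, the text should say so and give the reason.

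Cost: a sentence and a uniform term. No new visits, patients or committee are needed, because the monitor already approves the move between dose levels. The downside is an occasional delayed or incomplete course of a vaccine that takes 12 months to make, and slightly less immune-response data: one such patient is 1 of at most 6 at a dose level (1/6 = 17%).

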Lymph Node Harvest/Biopsy – in patients whose LPL presents primarily as lymphadenopathy, and who lack significant bone marrow involvement (< 10%), a safely accessible lymph node, measuring at least 1.5 cm in the long axis, will be harvested in lieu of the bone marrow aspirate and collected in sterile saline. One third of the specimen will be used for morphological classification and immunophenotypic characterization. Two-thirds of the specimen will be used to provide starting material for manufacture of the vaccine, and sent to the UTMDACC Lymphoma/Myeloma Core laboratory and assigned a unique accession number. Should the first lymph node sample not provide sufficient tumor cells for the vaccine production and immunologic assays, a second excisional lymph node biopsy may be performed to reach the needed yield.

If pathologic lymphadenopathy or hepatosplenomegaly were noted on CT scan imaging during the Research Eligibility Evaluation (REE) OR there is clinical concern for development of enlarged lymph nodes/organomegaly compared with scans performed for the REE, the following restaging imaging will also be performed within 1 week of receiving the 1st dose of vaccine to serve as the baseline for subsequent comparison; CT scans of Neck, Chest, Abdomen and Pelvis. Unless clinically indicated, this imaging will only be obtained if it has been ≥6 weeks since scans were performed for the REE.

On study evaluations are indicated in Table 1, and should occur within 48 h prior to each vaccination. Toxicities documented on the day of the first vaccination (prior to receipt of the vaccine) will serve as the baseline assessment. For immunological studies 10 ml peripheral blood for serum and 30 ml for peripheral blood mononuclear cells (PBMC) isolation will be collected within 2 days prior to day 1 of each vaccination. There is a +/− 5 business day window for all the following events: post-vaccine therapy evaluations at 4 weeks after the last vaccination and every 2 months thereafter for a year; re-staging CT scans of the neck, chest, abdomen and pelvis at 4 weeks after the final vaccination and every 6 months thereafter for a year; collection of 10 ml peripheral blood for serum for storage and 60 ml for PBMC isolation at 4 weeks after the last vaccination and every 4 months for 1 year thereafter for immunological studies.

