### Risk/benefit assessment

The primary objective of the study is to provide safety data on a personalized lymphoma DNA vaccine (scFv-CCL20 plasmid) administered by an intradermal needle-free injection device in small cohorts of asymptomatic LPL patients. Study risks include but are not limited to injection site reactions and transient flu-like symptoms. The primary endpoint of the study will be the determination of the MTD of scFv-CCL20. This information can be used to design future trials that seek to determine the efficacy of intradermal administration of this DNA vaccine in the treatment of asymptomatic LPL.

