## Discussion

At the time of this writing, the first 6 patients have been enrolled and treated. Based on our IND-enabling animal toxicology studies with this DNA vaccine and past experience with other idiotype protein vaccines, we do not expect any Grade 3 or 4 toxicities. We anticipate that both doses will be well tolerated and the 2500 μg dose is likely to be chosen to evaluate the efficacy of the vaccine in a future phase 2 clinical trial.

The ideal patient population to benefit from this treatment strategy would be previously untreated LPL patients who are at high risk of early disease progression. While patient selection is outside the scope of this current phase 1 safety study, we fully anticipate incorporating eligibility criteria in a subsequent phase 2 clinical trial, which would select for such high-risk patients.

Finally, we expect that the absolute numbers of immunosuppressive cells in the pre-vaccine samples will likely correlate inversely with the quality and magnitude of the tumor/peptide-specific T cell responses and that such effector T-cell responses are likely to be higher in patients receiving the higher dose of the vaccine compared with the lower dose. We hypothesize that post-vaccination we will observe increased CD8^+^ (and CD4^+^) to FoxP3^+^ ratios and decreases in PD-1 and CTLA-4 expression by T cells. We expect to see an increased number and density of effector T cells interacting with LPL tumor cells, associated with vaccination. These results could inform the future development of new molecular biomarkers.

Further, the analysis of the secondary objectives will provide a preliminary readout of the biologic activity of the vaccine and will likely be hypothesis-generating. We expect to find imbalances in patients’ characteristics because this is an early phase, small size, and non-randomized trial. The data from these analyses will provide insight for, and assist in the design of, future studies even though the statistical power for the analysis will be limited, especially for smaller effects/differences. The immunogenicity data may also provide guidance on alternative vaccine formulations using other adjuvants or combinations with immune checkpoint inhibitors in future clinical trials, particularly if decreases in immune regulatory molecule expression are observed post-vaccination, or if robust effector immune responses are observed, but with only modest clinical responses.

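### The only stated DLT evaluation falls before the second of three vaccinations, and the protocol does not say whether later DLTs count toward the MTD

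*Protocol article*

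**What the plan says.** Study design: "Patients will receive a series of 3 vaccinations at 4-week intervals (weeks 0, 4 and 8"). Study procedures adds that on-study evaluations "should occur within 48 h prior to each vaccination", so the week-4 evaluation comes before vaccination 2.

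Statistical plan, on timing: the first three patients at dose level 1 are "evaluated for DLT at the end of the first cycle (4 weeks"). No other DLT evaluation time appears in the article.

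Statistical plan, on content: "DLT is defined as follows: ≥ grade 2 allergic reaction, ≥ grade 2 autoimmune reaction and any grade 3 or 4 toxicity except for fever". A further item covers grade 4 fever that leads to a halved dose.

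Statistical plan, on the decision: "the MTD is defined as the highest dose level in which 6 patients have been treated with less than 2 instances of DLT". Neither this sentence nor the rule for stopping the protocol at the lower dose gives a period over which DLTs are counted.

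Risk/benefit assessment: "The primary endpoint of the study will be the determination of the MTD of scFv-CCL20".

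Events after week 4 are collected. Table 1 has AE/SAE recording at every visit from baseline on, and Safety and adverse events captures SAEs to 30 days after the last treatment. The toxicity paragraph of Study design sets out when an individual patient's later vaccinations are withheld or reduced. The Statistical plan tabulates toxicity by type and severity.

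**The concern.** The treatment under study is a three-vaccination course, but the one DLT evaluation time stated covers a single vaccination. The MTD sentence is silent on the window, so two analysts could take the same six patients and reach different answers. One would apply the 4-week evaluation throughout; the other would count every DLT recorded over the course. That ambiguity sits in the primary endpoint.

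It matters for this product because the DLT list includes allergic and autoimmune reactions from grade 2 upward. The vaccine is given repeatedly to provoke an immune response, through a fusion with a human chemokine, and such reactions could plausibly first appear on repeat exposure. If they did, a dose could be declared the MTD with two or more of six patients having had a DLT-type event after vaccination 2 or 3.

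**Working it through.** **The plan's own figure.** Two dose levels × 6 patients = 12, which agrees with "Given 2 predefined dose levels, it is anticipated that up to 12 eligible patients are required". Lengthening the DLT window does not change this maximum.

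**Timeline.** Vaccinations fall at weeks 0, 4 and 8. The DLT evaluation is at week 4, before vaccination 2. The post-vaccine visit is 4 weeks after the last vaccination: 8 + 4 = week 12. The stated window thus holds one of three vaccinations, and a full-course window would end 12 − 4 = 8 weeks later.

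**Inputs.** The MTD rule (6 treated, fewer than 2 with DLT) and the number of vaccinations come from the article. The DLT risks p1, p2 and p3 at vaccinations 1, 2 and 3 are not given, so they are assumptions here, taken as independent between vaccinations and patients.

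**Formulas.**
- Risk over the course: c = 1 − (1 − p1)(1 − p2)(1 − p3).
- Chance that a dose meets the rule at patient-level risk p: P(p) = (1 − p)^6 + 6p(1 − p)^5. Stopping early at two or more DLTs in the first three patients does not alter this, because such a dose has already failed.

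**Worked case, 10% at each vaccination.**
- c = 1 − 0.9^3 = 0.271.
- 4-week count: P(0.10) = 0.886.
- Full-course count: P(0.271) = 0.729^6 + 6 × 0.271 × 0.729^5 = 0.150 + 0.335 = 0.485.
- Share of the course risk outside the stated window: (0.271 − 0.10)/0.271 = 63%.

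**Range of assumptions.**

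| Risk at vaccinations 1/2/3 | Course risk | Meets rule, 4-week count | Meets rule, full-course count |
|---|---|---|---|
| 1/1/1% | 3.0% | 0.999 | 0.988 |
| 2/2/2% | 5.9% | 0.994 | 0.956 |
| 5/5/5% | 14.3% | 0.967 | 0.794 |
| 10/10/10% | 27.1% | 0.886 | 0.485 |
| 5/10/20% | 31.6% | 0.967 | 0.386 |
| 15/2/2% | 18.4% | 0.776 | 0.695 |

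The gap is negligible when the vaccine is very safe, modest when risk sits mainly at the first vaccination, and large when the risk is moderate at each vaccination or rises with repetition.

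**The case against.** The strongest reply is that the 4-week sentence describes only the first look of the 3 + 3 scheme, in the first three patients at dose level 1. The MTD and lower-dose stopping sentences have no time limit, and the fever item looks ahead to later vaccinations. An early look with an unrestricted final count is a possible reading. This stands, and it rules out a stronger claim that a reader might infer: that the protocol restricts DLT to the first vaccination and the MTD therefore cannot cover the course. The text does not settle the matter either way. But no sentence extends the window, and the only time stated is 4 weeks.

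Second, later toxicity is not lost. It is graded at each visit, tabulated, and can end or reduce an individual's vaccinations. A medical monitor must also approve a cohort summary before the dose is advanced. This stands too, so it would be wrong to say that late events go unseen. What is lacking is a stated link from those events to the MTD count. The cohort summary is a review with no rule for late events and no requirement that all three vaccinations be complete.

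Third, the article anticipates little toxicity: "we do not expect any Grade 3 or 4 toxicities". Nothing in it says that allergic or autoimmune reactions are expected after vaccination 2 or 3, so repeat-exposure toxicity is a possibility and not a prediction. If risks are as low as the authors hope, the two counts nearly always agree. The definition still has to work if that hope fails, and grade 2 allergic or autoimmune reactions are DLTs outside the quoted expectation.

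**Conclusion.** The point holds as an ambiguity in the primary endpoint. The one stated DLT evaluation time precedes vaccination 2, the MTD and lower-dose stopping rules have no window, and the article does not say whether recorded DLT-type events after vaccinations 2 and 3 count. Applied with the stated window, the rule can pass a dose on one third of the course.

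The size depends on risks that the article does not give. Under independence, the drop in the chance of meeting the rule when the full course is counted runs from about 0.01 (1% per vaccination) through 0.17 (5%) to 0.40 (10%), and is 0.08 when risk is mostly at the first vaccination. These figures are illustrations, not forecasts. The timing mismatch rests on the article's own schedule and needs none of them.

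**What to change.** For the final MTD determination, count patients with a DLT from the first vaccination through the existing visit 4 weeks after the third. State that the week-4 evaluation is the interim look. For patients already treated (six, according to the Discussion), full-course counts can be derived from the graded adverse events collected at each visit.

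Separately, reconcile Study design, its toxicity paragraph and the Statistical plan, so that they say whether events after vaccinations 2 and 3 count toward escalation and toward the lower-dose stopping rule. Which rule applies there is for the sponsor to decide; the text needs to give one answer.

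The cost is an amendment to the wording of the primary endpoint after patients have been treated, and a final MTD declaration up to about 8 weeks later. That is short beside the 12 months stated for vaccine preparation. No visits or patients are added, and the maximum stays at 12.
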